**Table 5: Summary of clinical studies using PM**

| Dose mg/kg/day        | Single Agent No. Patients | Place                     | Combination Therapy with SSG No. Patients | Place                                   |
|-----------------------|---------------------------|---------------------------|-------------------------------------------|-----------------------------------------|
| 6                     |                           |                           | 40                                        | India (Thakur)                          |
| 12                    | 60                        | India (30 Jha, 30 Thakur) | 120                                       | India (96 Thakur, 24 Thakur)            |
| 14-16                 | 19                        | Kenya (Chunge)            | 124                                       | Kenya and Sudan (23 Chunge, 101 Seaman) |
| 16                    | 60                        | India (30 Jha, 30 Thakur) |                                           |                                         |
| 18                    |                           |                           | 50                                        | India (Thakur)                          |
| 20                    | 60                        | India (30 Jha, 30 Thakur) |                                           |                                         |
| Total Patients | 199                |                           | 384                                |                                         |

## **TRIAL OBJECTIVES AND PURPOSE**

Currently in the three countries, Sudan, Kenya and Ethiopia many of the patients present themselves in remote areas and need to be treated in relative resource poor settings. It is for this reason that standardised treatment with proven efficacy is much needed. A shorter course of treatment is not only advantageous for the patient but also reduces the overall case load in the clinics thus reducing the risk of disease outbreaks in already immuno-compromised kala-azar patients. Paromomycin, either alone or in combination with SSG would decrease the treatment duration substantially. An additional added value of combination therapy is that it is likely to reduce the chances of development of parasite resistance against the individual drugs.

Leishmaniasis experts in the three countries are in agreement that there are potential benefits of the combination treatment of SSG and PM and that its efficacy should be evaluated with the view to introduce this protocol if proven efficacious and safe. There is ample circumstantial evidence of the use of this combination therapy and its efficacy and tolerability as a standardized protocol. This can only be confirmed through a randomised controlled study with 6 months follow up.

## **HYPOTHESIS**

That a combination course of SSG and PM (17 days) is similar in efficacy to either PM alone(21 days) or SSG alone (30 days) and that the shorter course combination (17 days) is not more toxic than PM or SSG alone.

## **OBJECTIVES OF THE TRIAL**

- 1) To assess the efficacy and safety of SSG 30 days alone in the treatment of patients with VL.
- 2) To assess the efficacy and safety of PM 21 days alone in the treatment of patients with VL.
- 3) To assess the efficacy and safety of SSG and PM as a combination course of 17 days in the treatment of patients with VL.

## **METHODOLOGY**

### **STUDY DESIGN**

This will be a multi-centre, prospective, open, parallel group, comparative trial of efficacy and safety of SSG alone given IM/IV (according to usual hospital practice) for 30 days versus paromomycin alone given IM for 21 days versus a combination of SSG and PM given for 17 days, in the treatment of patients suffering from VL in Ethiopia, Kenya and Sudan.

Patients who have clinical symptoms and a confirmed parasitological diagnosis of VL by splenic aspirate, lymph nodes aspirate or bone marrow aspirate (to be specified for each hospital site) and who have fulfilled the inclusion/exclusion criteria will be enrolled.

The primary endpoint will be cure rate at 6 months post treatment. Secondary endpoints will be cure rate at end of treatment (Day 31 for SSG, Day 22 for PM, Day 18 for PM + SSG) and at three months post treatment.

### **INCLUSION CRITERIA**

Patients who fulfill the following inclusion criteria will be enrolled into the study:-

- 1) Patients for whom written informed consent has been signed by the patients themselves (if aged 18 years and over) or by parents(s) or legal guardian for patients under 18 years of age.

## **FINAL VERSION LEAP 0104 31 JULY 2004 CONFIDENTIAL**

- 2) Patients aged between 4 and 60 years (inclusive) who are able to comply with the protocol. It is justified to include children because they represent more than 50% of VL cases.
- 3) Patients with clinical signs and symptoms of VL and diagnosis confirmed by visualization of parasites in tissue samples (spleen, lymph node or bone marrow) on microscopy.

### **EXCLUSION CRITERIA**

Patients with the following will be excluded from the study:

- 1) Patients who have received any anti-leishmanial drug in the last 6 months.
- 2) Patients with a negative splenic / lymph node / bone marrow smears.
- 3) Patients with a clinical contraindication to splenic/lymph node/ bone marrow aspirates.
- 4) Patients with severe protein and or caloric malnutrition (Kwashiorkor or marasmus)
- 5) Patients with previous hypersensitivity reaction to SSG or aminoglycosides.
- 6) Patients suffering from a concomitant severe infection such as TB or any other serious underlying disease (cardiac, renal, hepatic) which would preclude evaluation of the patients response to study medication.
- 7) Patients suffering from other conditions associated with splenomegaly such as schistosomiasis.
- 8) Patients with previous history of cardiac arrhythmia or an abnormal ECG
- 9) Patients who are pregnant or lactating.
- 10) Patients with haemoglobin < 5gm/dl.
- 11) Patients with WBC <  $1 \times 10^3/\text{mm}^3$ .
- 12) Patients with platelets < 40,000/ $\text{mm}^3$ .
- 13) Patients with liver function tests more than three times the normal range
- 14) Patients with serum creatinine outside the normal range for age and gender
- 15) Patients with pre-existing clinical hearing loss.

#### **NB**

Relevant tests will be done to exclude the above listed conditions.

### **HIV-status and VCT**

All patients will be offered counseling and screening for HIV (voluntary counseling and testing programme (VCT)). This may either be done at the same

## **FINAL VERSION LEAP 0104 31 JULY 2004 CONFIDENTIAL**

time as consent is obtained for inclusion in the trial or at a later date according to hospital practice. HIV positive patients will not be excluded from the clinical trial. Subset analysis will be performed to assess any differences in response.

### **CRITERIA FOR PATIENT WITHDRAWAL**

Patients will be considered to have completed the study if they satisfy all entry criteria, complete the course of treatment and attend the 6 month follow-up visit.

Patients will be considered to have withdrawn from the study if they had entered into the study (i.e. gave informed consent and received at least one day's treatment) but did not complete the treatment period and follow up period.

Treatment failure will be defined as no change or an increase in the patient's disease severity i.e. in signs and symptoms of VL, and parasitology, such that the patient is withdrawn from the study and alternative therapy given.

A patient may be withdrawn from the study at any stage if the investigator or the DSMB considers there is a serious risk to the patient from continuation in the protocol. Alternative therapy will be provided to the patient if needed, upon withdrawal from the study.

A patient may withdraw, or be withdrawn, from the study for one of the following reasons:

- Serious adverse events (drug related or not)
- Deviation from protocol (including non-compliance)
- Lost to follow-up
- Termination by the sponsor
- Withdrawal of consent

The reason for termination will be recorded on the CRF. Patients withdrawn from the study will be followed-up at 3 and 6 months for monitoring of adverse events wherever possible. Every effort will be made to follow up withdrawn patients in order to determine the final outcome. This information will be recorded in the CRF and these patients data will be analysed as those who failed to respond to treatment.

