#### **Analysis**

In the analytical approach intention to treat will be used. The aim is to estimate the difference in treatment outcomes for the three arms. The intention to treat analytical method will take care of events such as patient withdrawal from the trial, failure to comply with treatment, change in treatment and lost to follow-up.

There are two basic options:

Analyse final outcome only for those who complied perfectly with each treatment

Analyse data for all subjects in the groups to which they were randomized. This is referred to as 'Intention to treat' analysis or the 'pragmatic approach'.

The second option will be adopted, analysis will be carried out according to the original treatment assignment regardless of adherence to treatment or protocol.

There will be no exclusion of patients or events. Drop-outs will be checked to establish whether they were systematic or non-random. The analysis will, as much as possible stick to the protocol to avoid data dredging as part of post ad hoc analysis.

Note: Specific country analysis will be of little value because it lacks power. The data will have to be pooled for it to achieve the necessary power in the efficacy analysis.

Summary statistical measures to be computed

The summary statistics will include the  $\chi^2$  and risk ratios per arm for the overall efficacy comparison. The analysis and interpretation will heavily rely on confidence intervals of the cure rates among the three arms of the RCT. Other estimations to be made will be the calculation of the power finally achieved by the trial. This will be followed by the presentation of the results in terms of basic descriptive statistics and statistical diagrams. Finally multivariate analysis will be carried out to establish the socio-demographic factors associated with the main parameters.

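### Withdrawn patients count as failures even when a clear 6-month smear is known, against the primary endpoint, and the compliers' analysis is declined despite a similarity aim

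*Protocol*

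**What the plan says.** The Protocol section Criteria for Patient Withdrawal treats as withdrawn anyone who received at least one day of treatment "but did not complete the treatment period and follow up period". The reasons listed include "Serious adverse events (drug related or not"), protocol deviation, loss to follow-up, "Termination by the sponsor" and withdrawal of consent. The section then says "Every effort will be made to follow up withdrawn patients in order to determine the final outcome", and continues: "This information will be recorded in the CRF and these patients data will be analysed as those who failed to respond to treatment".

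The section Primary Efficacy Endpoint defines the primary variable differently, as parasitological clearance on a smear six months after treatment. It makes no exception for withdrawn patients.

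The Analysis section names two options, perfect compliers only or all patients as randomised. It decides: "The second option will be adopted, analysis will be carried out according to the original treatment assignment regardless of adherence to treatment or protocol". It adds: "There will be no exclusion of patients or events".

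The aim is similarity. Under Hypothesis, the combination "is similar in efficacy to either PM alone(21 days) or SSG alone (30 days"), and lack of greater toxicity is a separate part of the same hypothesis. Sample size Determination likewise takes the absence of a clinically relevant difference as the alternative hypothesis.

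**The concern.** The plan seeks and records an outcome and then overrides it. A patient withdrawn for an unrelated event, never given another anti-leishmanial drug and smear-negative at six months gets two opposite classifications from two sections of one protocol. The withdrawal section's own definition of treatment failure requires unchanged or worse disease leading to alternative therapy, and this patient meets no part of it.

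The result is an efficacy endpoint that also counts toxicity, non-compliance and administrative events. Treatment is open-label and lasts 17, 21 or 30 days depending on the arm, so neither the frequency nor the cause of withdrawal need be the same across arms. The bias can then go either way.

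Two further points follow. For a similarity claim, an ITT analysis alone is not reliably conservative, yet the protocol names the compliers' analysis and declines it. The sample size is also inflated as if lost patients leave the analysis, whereas the analysis rules keep them in as failures.

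**Working it through.** **Inputs from Sample size Determination.** Cure rates of 95% and 85%, power 90%, two-sided 5%, k = 10.5, equal allocation, 15% attrition.

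**The protocol's own figure.** 10.5 × (0.85 × 0.15 + 0.95 × 0.05) / 0.10² = 10.5 × 0.175 / 0.01 = 183.75, so 184 per arm. Then 184 / 0.85 = 216.5, so 217. Both figures reproduce. Dividing by 0.85 is right if the lost 15% leave the analysis: 184 completers per arm give chi-square power of 89.5%.

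**Assumptions added here.** Withdrawal is independent of true cure. A fraction w of each arm is withdrawn and all are scored as failures. The similarity margin is taken as 10 points, because the protocol gives 10 points as the effect sought and states no margin.

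**Formulas.**
- Scored cure = true cure × (1 − w).
- Chi-square power = Φ{[d − 1.96 √(2p̄(1−p̄)/n)] / SE}, with SE = √{[p₁(1−p₁) + p₂(1−p₂)]/n}, d the difference in cure rates and p̄ their mean.
- Chance of declaring similarity = Φ{(0.10 − d)/SE − 1.96}, one-sided at 0.025.

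**Worked case, w = 15%, n = 217.**
- Scored rates: 0.95 × 0.85 = 80.75% and 0.85 × 0.85 = 72.25%, so d = 8.5 points.
- SE = √[(0.1554 + 0.2005)/217] = 0.0405.
- Power: p̄ = 0.765, so (0.085 − 1.96 × 0.0407)/0.0405 = 0.13, giving 55.1%.
- False similarity: 0.015/0.0405 − 1.96 = −1.59, giving 5.6%.
- Both arms truly 95%: SE = √(2 × 0.1554/217) = 0.0379, and 0.10/0.0379 − 1.96 = 0.68, giving 75.2%.

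| Withdrawn, each arm | Scored cure | Difference (points) | Chi-square power | False similarity | Similarity shown if both truly 95% |
|---|---|---|---|---|---|
| 0% | 95.0% v 85.0% | 10.0 | 93.7% | 2.5% | 99.8% |
| 5% | 90.25% v 80.75% | 9.5 | 80.5% | 3.5% | 94.0% |
| 10% | 85.5% v 76.5% | 9.0 | 66.7% | 4.5% | 84.1% |
| 15% | 80.75% v 72.25% | 8.5 | 55.1% | 5.6% | 75.2% |

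With 235 per arm (705/3, from the site table) the pattern is the same: at 15%, power is 58.5% and false similarity 5.8%.

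**Unequal withdrawal.**
- 15% in the 95% arm and 5% in the 85% arm: 0.95 × 0.85 = 80.75% and 0.85 × 0.95 = 80.75%. The 10-point deficit vanishes and false similarity is 75%.
- 5% in the 95% arm and 15% in the 85% arm: 90.25% against 72.25%, an 18-point gap.
- Both arms truly 95%, withdrawal 5% and 15%: 90.25% against 80.75%, a 9.5-point difference created by the rule.

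**Sample-size mismatch.** With the 15% kept in as failures in both arms, the protocol's formula at the scored rates gives 10.5 × 0.3559 / 0.085² = 517.3, so 518 per arm against the planned 217.

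**The case against.** Scoring non-completers as failures is a recognised, pre-specified composite. Many withdrawn patients may receive alternative therapy, and for them failure is defensible. That stands, and the fix keeps it. The Analysis section also plans to check whether drop-outs are systematic. This could reveal unequal withdrawal, but it does not change how anyone is scored. Supporting analysis sets are often left to an SAP, but here the protocol itself names the compliers' analysis and rejects it.

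A reader might infer that the rule necessarily pulls the arms together and so favours a similarity claim. The documents do not support that. Equal withdrawal shrinks the difference in cure rates but leaves the cure risk ratio, a measure the Analysis section names, at 0.85/0.95 = 0.7225/0.8075 = 0.895. More withdrawal in the worse arm separates the arms. The rise in false similarity is modest when a confidence interval is set against a margin, and the larger loss is in showing similarity that is real.

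A reader might also infer that the 30-day course must hand the 17-day combination a large spurious advantage. The protocol's own tables point to a small effect. Under Dose finding Studies, the 28-day antimonial arms had 0/30, 0/30 and 4/50 non-completers: 4/110 = 3.6%, or about 0.13% per day. At that rate, non-completion is about 2.2% by day 17 and 3.9% by day 30. At an assumed 90% cure the gap is about 0.9 × 1.7 = 1.5 points. Recorded defaulters show no duration pattern (2/110 on 28-day antimonial, 5/180 on 21-day paromomycin alone), and trial patients are in hospital during treatment. Sponsor termination is listed only as a reason for withdrawal. No rule for closing a single arm is described, so nothing can be sized from it.

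**Conclusion.** The concern holds as a conflict between sections and a weak analysis rule. A withdrawn patient with no other anti-leishmanial drug and a clear 6-month smear is classified in opposite ways by Primary Efficacy Endpoint and Criteria for Patient Withdrawal, and non-efficacy events enter the cure rate. The direction of bias is not fixed.

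For equal withdrawal at 15%, the effect is at most a fall in chi-square power from about 94% to 55%, a rise in false similarity from 2.5% to 5.6%, and a fall from 99.8% to 75% in the chance of showing true similarity at 95% cure. These figures rest on 217 per arm, withdrawal independent of cure, and an assumed 10-point margin. They are upper bounds on what the fix could recover at that rate, because the protocol's 15% is loss to follow-up and patients truly lost have no result to restore. Unequal withdrawal is outside that bound and could hide or create a difference. The mismatch between the attrition inflation and the failure rule stands whichever scoring is kept. The change should be made, but the finding does not show that the trial favours any arm.

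**What to change.** - Reconcile Criteria for Patient Withdrawal, Primary Efficacy Endpoint and Analysis: a withdrawn patient with a known 6-month parasitological result and no other anti-leishmanial drug is analysed by that result.
- Keep failure scoring for patients given other anti-leishmanial therapy and, as the simple default, for those whose outcome is unknown.
- Report all-withdrawn-as-failure as a sensitivity analysis.
- In Analysis, add a per-protocol analysis beside ITT because the aim is similarity. It can be judged formally only once a margin is stated.
- In Sample size Determination, align the attrition adjustment with the scoring rule, separating patients expected to have an unknown outcome from those withdrawn with a known result.
- State whether the 6-month aspirate planned for all patients applies to withdrawn patients, since the withdrawal section describes their visits as adverse-event monitoring wherever possible.

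The cost is wording, one more analysis set, and two analyses that should agree before similarity is claimed. Aligning the attrition adjustment may show that more patients are needed. The 518 per arm above is the extreme case under the protocol's difference formula, so the expected share with unknown outcome should be stated before any new figure is set.

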### **Randomization in the Clinical Trial (RCT)**

The multi-country study adopted restricted randomization in a three-arm study per country. This approach prevents the potential pitfall/imbalance in study numbers that could have resulted if one used simple random sampling. In order to avoid manipulation of blocks of small sizes, blocks of size 15 will be used in randomization. This approach ensures that the study balances after the 15th patient. In the allocation of the drugs to the patients concealment will be used in order to minimize selection bias. Opaque envelopes will be numbered sequentially and then sealed. This process will be carried out at the coordinating centre at KEMRI.

[figure not shown]

Fig 1: The structure of the RCT

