## **SUMMARY**

Visceral leishmaniasis (VL) or Kala-azar is the most severe form of leishmaniasis. It is estimated that 500,000 new cases world wide of VL are diagnosed annually. 90% of VL cases occur in developing countries: India (especially Bihar), Bangladesh, Nepal, North Eastern Brazil and Sudan. For the past 100 years, antimony has been the first line of treatment for VL cases despite considerable toxicity and the requirement for 4 weeks hospitalization.

Resistance to antimony coupled with emergence of HIV associated with VL is on the increase. New and improved treatment options are urgently needed to replace or complement the few currently available drugs. The wide variety of epidemiological situations and clinical presentations of this disease further warrant a series of treatment options instead of one single treatment or control strategy for the affected populations.

During 2003, experts in VL together with representatives of regulatory authorities and health ministries from Kenya, Ethiopia and Sudan met (Nairobi, May 2003, Khartoum, August 2003) to discuss the development of new treatment options for this fatal but neglected disease.

This research proposal will be a multicentre, prospective, open label, parallel group, comparative trial to determine the efficacy and safety of sodium stibogluconate (SSG) 20mg/kg/day given for 30 days, Paromomycin (PM) 15mg/kg/day for 21 days, and a combination of SSG and PM, 20mg/kg/day, 15mg/kg/day respectively, given for 17days in the treatment of patients suffering from VL in Ethiopia, Kenya and Sudan. Primary endpoint will be cure rate at 6 months.

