### **PRIMARY EFFICACY ENDPOINT**

The primary efficacy variable is parasitological clearance at 6 months post treatment by splenic, lymph node, or bone marrow smear.

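### In this open-label trial one disclosed block size of 15 leaves some allocations predictable, and no masked reading is specified for the primary-endpoint smear

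*Protocol*

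**What the plan says.** The Summary and the Study Design section both describe open treatment; the latter reads "This will be a multi-centre, prospective, open, parallel group, comparative trial".

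The section on randomization sets out "restricted randomization in a three-arm study per country" and gives the block size with its reason: "In order to avoid manipulation of blocks of small sizes, blocks of size 15 will be used in randomization". It adds: "This approach ensures that the study balances after the 15 th patient". On concealment it says that "concealment will be used in order to minimize selection bias", and describes the means: "Opaque envelopes will be numbered sequentially and then sealed". The envelopes are prepared at the coordinating centre.

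Under Sample size Determination, allocation is equal across the three arms. The table by team rounds each of five teams to complete blocks of 15. Sudan and Ethiopia have two teams each.

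The primary endpoint is "parasitological clearance at 6 months post treatment by splenic, lymph node, or bone marrow smear". The efficacy sections give the sampling days, the source of the aspirate and the maximum number of aspirates. They do not say who reads the slides or whether the reader knows the arm.

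**The concern.** A sealed opaque envelope stops staff from seeing the next assignment. It does not stop them from counting. With open treatment every past assignment is known. With one block size written in the protocol, the point at which the arms balance is known too. Towards the end of a block the remaining assignments can be narrowed down, and the last is always certain.

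Foreknowledge matters only if staff can act on it, and the protocol leaves some room. A patient with a co-infection is treated first and re-assessed after one week, so the time of entry can move. Exclusion criterion 6 calls for judgement. HIV testing may take place when trial consent is obtained, so a factor that the protocol expects to affect cure may be known before the envelope is opened. Selection bias is the very thing that the protocol says its concealment should minimise.

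The second half concerns the outcome. The protocol confirms the baseline diagnosis by microscopy, and the primary endpoint is again a smear. If the reader knows the arm, judgement on a doubtful slide can follow expectation. Masked reading is one of the few protections available to an open trial, and it has to be organised before slides are made, so it belongs in the protocol rather than only in an analysis plan.

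**Working it through.** **The plan's own figures.** The protocol gives no figure for predictability. Its team table reproduces: 60 + 150 + 225 + 150 + 120 = 705, or 4 + 10 + 15 + 10 + 8 = 47 complete blocks of 15.

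**Assumptions.** Each block holds 5 patients per arm (three arms, equal allocation, block of 15). The observer knows the block size and where blocks start, and sees every earlier allocation in the sequence.

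**Allocations known with certainty.** The next allocation is certain once two arms are used up, so the expected number per block is the mean length of the run of identical assignments at its end. For n = 15 and m = 5 per arm this is n / (n − m + 1) = 15 / 11 = 1.36, and 1.36 / 15 = 9.1%. Over 47 blocks: 47 × 15 / 11 = 64.1.

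**Allocations with at least one arm ruled out.** For a given arm, the expected number of positions after its last use is 10 / 6 = 1.667. Three arms give 5. Positions where two arms are used up are counted twice, so subtract 1.364: 5 − 1.364 = 3.636 per block, and 3.636 / 15 = 24.2%, about 171 of 705. The 64 lie within the 171 and must not be added to them.

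**Best guess.** Exact enumeration, always guessing the arm with most places left, gives a hit rate of 49.7%, against 33.3% by chance.

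**What the choice of 15 already achieves**

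| Fixed block size | Certain | Best guess correct |
|---|---|---|
| 3 | 33.3% | 61.1% |
| 6 | 20.0% | 56.1% |
| 9 | 14.3% | 53.2% |
| 12 | 11.1% | 51.2% |
| 15 | 9.1% | 49.7% |

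**If a sequence is shared.** Suppose two teams share one country sequence equally, each sees only its own patients, and each knows where blocks start (assumptions; the protocol does not say). Simulation then gives a best-guess rate of about 40% and almost no certain allocations.

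**Varying blocks.** These were simulated with sizes drawn at random and an observer who knows the set of sizes but not the current one:

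| Block sizes | Certain | Best guess correct |
|---|---|---|
| 15 fixed | 9.1% | 49.7% |
| 9, 12, 15 | about 1.9% | about 51% |
| 12, 15, 18 | about 1.5% | about 49% |
| 15, 18, 21 | about 1.3% | about 48% |

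Varying the size removes most of the certainty. It lowers the best-guess rate only if it does not bring in smaller blocks, and then only a little.

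**Smear reading.** No arithmetic applies. The protocol gives no reading-error rate and nothing from which a difference in error between arms could be derived. The 6-month visit falls at the same time after treatment in every arm, so a coded slide need not reveal the arm. The end-of-treatment smear, a secondary endpoint, is taken on day 18, 22 or 31 depending on arm, so there the day itself can reveal it.

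**The case against.** The protocol thought about this risk. It chose a large block expressly against manipulation and specified numbered, opaque, sealed envelopes prepared centrally. The table of fixed sizes shows that the choice works: a block of 3 would make a third of allocations certain. Varying blocks are therefore a refinement of a reasoned choice, not the correction of an error. This stands, and it keeps the allocation half of the point small.

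Three stronger readings are tempting, and the protocol does not support them:

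- **Sites can deduce their upcoming allocations.** With certainty this holds for about 9% at most, and only where one group of staff sees the whole sequence. The wording by country and the rounding by team leave that open.
- **The block size is public.** The protocol is marked confidential. The size is disclosed to those who hold the protocol, which is enough for the concern but is not publication.
- **The smears are read unmasked, with a known effect on the result.** The visible text is silent; it does not say that readers know the arm. A section between Study Design and Inclusion Criteria and the randomisation figure could not be seen. One can assume that 3% of one arm is misread in one direction and conclude that the difference moves by 3 of the 10 points sought, but that only returns the assumption.

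It can also be said that silence on slide reading is not an error. For a smear-based primary endpoint in an open trial, however, masked reading is a basic control of bias, and sections that go into detail on aspirates are where it would be stated.

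**Conclusion.** The point holds in a limited form. With one disclosed block size and open treatment, up to about 9% of allocations (at most about 64 of 705) could be known in advance, and for up to about 24% at least one arm could be ruled out. Both figures assume an observer who sees the complete sequence and keeps count, and both fall if teams share a sequence. They measure opportunity; nothing in the protocol shows that anyone would use it.

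No masking is specified in the visible text for reading the primary-endpoint smear. This is the weightier half, because it touches the primary outcome of every patient who is read, but its effect cannot be quantified from the protocol.

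The sample-size calculation is not affected. The changes are worth making because they serve the protocol's own aim and need no extra patients or procedures on patients.

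**What to change.** Before the start:

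1. Generate the list with randomly varying block sizes no smaller than the present one, for example 15, 18 and 21. Do not use 9, 12 and 15, which would not lower the best-guess rate.
2. Keep the sizes at the coordinating centre and take them out of the protocol that sites hold.
3. State whether the sequence runs by country or by team, and align the randomization section with the team table.
4. Label slides with a code that hides arm and visit day, and have the microscopist read them without access to the treatment sheet.

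The cost is a new randomisation list and a slide-coding step. Arm totals may be slightly unequal at the end, and team targets will no longer fall on exact multiples of a block. Informed guessing remains at about 48%, and end-of-treatment slides may still be guessable from the day on which they are taken.
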